### Demographic variables and descriptive

We will record the following variables: age, living alone (yes/no), BMI, smoking (yes/no), are you afraid of falling (yes/no), have you fallen the last year (yes/no), injuries caused by falls the last year, number and name of medications, taking analgesics (yes/no), pain level last week by score from 0 to 10 on a Numeric Rating Scale [30, 31] and comorbidities.

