SFT is a valid and reliable test for physical fitness [41] designed to assess underlying physical components associated with mobility in older people, such as muscle strength, aerobic endurance, flexibility, body composition (assessed as BMI in kg/m2) and agility/dynamic balance [42]. The test consists of: number of Chair Stands in 30 s, number of Arm Curls in 30 s, Chair-Sit-and-Reach-Test (CSRT) (cm), Back Scratch Test (cm), 2.45 m Up-and-Go test (seconds) and 6 min walk test (6 MWT) and BMI (weight/height^2^). All of the tests have high reliability and validity and the procedures for administering SFT are standardized and described in detail [41, 42]. The CSRT was excluded due to safety reasons for our study population, as it requires flexion of the back. The 6 MWT will of practical reasons be performed walking around a 40 m course. In a study from Sciurba et al. [43] there was reported no significant difference between walking courses of 15 to 50 m.

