### Sample size estimation

The sample size is based on a substantial meaningful change in 10 m habitual walking speed [50]. Perera [50] defined the minimal detectable change as 0.05 m/s. A substantial meaningful change is defined as 0.10 m/s and the expected standard deviation in habitual walking speed is assumed to be 0.2 m/s based on findings by Perera [50]. This estimate requires 128 patients, 64 in each group, to obtain 80% statistical power with 5% significance level for an independent samples t-test. We will aim to include 150 in order to compensate for an estimate of 20% drop outs.

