### Statistical procedure

The results of the study will be reported in accordance with CONSORT [51]. Statistical analysis is performed using statistical software as e.g. SPSS, Stata or R. The level of significance is 5%. Descriptive data will be reported as mean (standard deviation), median (range) or count (percent) as appropriate. The data will be analysed following the intention-to-treat principle. Between group differences in primary and secondary outcomes at 3 months follow-up will be assessed using linear regression models with respective outcome at baseline as covariate and the randomised group as factor (dummy variable), i.e. an ANCOVA analysis [52]. In addition, we will perform linear mixed model analysis for repeated measurements. We expect few or none missing data in baseline characteristics. However, due to possible drop-outs or participants unable to complete the outcome measurements, there might be missing data for both primary and secondary outcomes during follow-up. Linear mixed model for repeated measurement is able to statistically adjust for missing data associated with variables in the model, i.e. missing at random (MAR) structure. Further, we will also assess multiple imputation methods and sensitivity analysis for missing data in longitudinal studies. All tests will be two-sided. A statistical analysis plan will be performed in advance of each paper from the study.

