### Limitations

Some limitations of this study should be noted. First, this study evaluates the programme in an urban area, which may limit its generalizability to rural parts and other states with varying demographic characteristics of older adult populations. Second, in this study we don’t recruit people with low walking speed in particular, and it therefore be less likely that we see an effect on the primary outcome. Furthermore, the Hawthorne effect should be considered [54]. Exercise intervention studies appeal to healthier and better-motivated individuals [55]. In this study the intervention is based on an exercise intervention of 12 weeks, twice a week. Frail women with osteoporosis and a history of vertebral fracture in particular may not be able to attend community-based classes twice a week, even though they might benefit even more than healthy women from an exercise intervention. Another limitation is the inclusion criteria, which restrict our findings to individuals living on their own and being free from severe cognitive symptoms. Again the frailest may not be included. General conclusions can only be drawn with caution and no conclusions about training results should be drawn beyond the female osteoporosis population with a history of vertebral fracture living at home. It is a risk of drop-outs and thereby missing data during follow-up. Impact of missing data will be assess with appropriate statistical methods as e.g. linear mixed models, multiple imputations and sensitivity analysis.

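### The 3-month ANCOVA for walking speed is valid, but could also adjust for age and the baseline 6-minute walk at no cost, for a modest gain in precision and some protection against unequal drop-out

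*Protocol article*

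**What the plan says.** Under Statistical procedure, the protocol article assesses group differences at 3 months, for primary and secondary outcomes alike, by "linear regression models with respective outcome at baseline as covariate and the randomised group as factor (dummy variable". No other covariate is named. The significance level is 5% and "All tests will be two-sided". The section adds a linear mixed model for repeated measurements, multiple imputation and sensitivity analysis for missing data. It lists no variables for these and announces a statistical analysis plan before each paper.

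Two further predictors are available:
- Age, under Demographic variables and descriptive: "We will record the following variables: age, living alone (yes/no), BMI".
- The "6 min walk test (6 MWT"), under Physical fitness, as part of the Senior Fitness Test. Outcome measures places the assessments at baseline, 3 and 6 months, with randomisation after the baseline assessment.

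Sample size estimation uses 0.10 m/s ("A substantial meaningful change is defined as 0.10 m/s") and an SD of 0.2 m/s, asks for 64 women per group "to obtain 80% statistical power with 5% significance level for an independent samples t-test", and recruits 150 to allow for 20% drop-out. Study design names no stratification factor, so none is missing from the model.

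**The concern.** One stopwatch-timed 10 m walk is an imperfect measure of walking ability. The 6-minute walk is a second, longer measure of much the same ability, and age is a plausible predictor as well. Both may predict 3-month speed beyond the single baseline walk. If so, the stated model leaves some precision unused.

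There is also a missing-data argument. An ANCOVA in women with a 3-month value is unbiased if drop-out depends only on arm and on the covariates in the model. The Discussion and Limitations sections say that frail women may struggle with the classes ("Frail women with osteoporosis and a history of vertebral fracture in particular may not be able to attend community-based classes twice a week"), and before 6 months only the exercise arm has classes to attend. If frailer exercise-arm women also missed the 3-month test, and frailty is only partly captured by baseline speed, the completers' comparison would lean towards exercise.

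**Working it through.** **Inputs from the protocol.** Difference 0.10 m/s, SD 0.2 m/s, two-sided 5%, 80% power, 64 per arm; 150 recruited, 20% drop-out. The minimal detectable change is given as 0.05 m/s.

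**Assumptions, none in the documents.** Correlation *r* of baseline with 3-month speed: 0.5 to 0.8. Share *q* of the variance left after baseline speed that age and the 6-minute walk explain together: 0.02 to 0.20.

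**1. The plan's own figure.** Standardised difference 0.10/0.2 = 0.5. The noncentral t gives 63.77, so 64 per arm, 128 in all, power 80.1%. The stated figure reproduces.

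**2. Evaluable women.** 150 × 0.8 = 120, or 60 per arm. An unadjusted t-test then has 77.5% power.

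**3. Precision.** SE = 0.2 × √[(1 − r²)(1 − q)] × √(2/60). At r = 0.7 and q = 0 this is 0.2 × √0.51 × 0.1826 = 0.0261 m/s. Adding the covariates multiplies the SE by √(1 − q). Power is from the noncentral t.

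| q | SE cut | SE, r = 0.7 (m/s) | Power at 0.10 m/s, r = 0.5 / 0.7 | Power at 0.05 m/s, r = 0.5 / 0.7 |
|---|---|---|---|---|
| 0 (stated model) | none | 0.0261 | 88.0% / 96.7% | 34.8% / 47.7% |
| 0.02 | 1.0% | 0.0258 | 88.7% / 97.0% | 35.4% / 48.5% |
| 0.05 | 2.5% | 0.0254 | 89.6% / 97.4% | 36.3% / 49.7% |
| 0.10 | 5.1% | 0.0247 | 91.1% / 98.0% | 38.0% / 51.8% |
| 0.15 | 7.8% | 0.0240 | 92.5% / 98.5% | 39.8% / 54.1% |
| 0.20 | 10.6% | 0.0233 | 93.9% / 98.9% | 41.8% / 56.6% |

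**4. What correlations would give such q?** Take age correlated −0.35 to −0.40 with baseline speed and −0.4 with the 6-minute walk, and q = (R² − r²)/(1 − r²).

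| 3-month speed with baseline speed / 6-minute walk / age | Baseline speed with 6-minute walk | q |
|---|---|---|
| 0.7 / 0.55 / −0.25 | 0.75 | 0.003 |
| 0.7 / 0.60 / −0.35 | 0.75 | 0.041 |
| 0.8 / 0.70 / −0.40 | 0.75 | 0.075 |
| 0.7 / 0.65 / −0.40 | 0.70 | 0.125 |
| 0.6 / 0.60 / −0.40 | 0.70 | 0.134 |

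The last row cuts the SE by 1 − √0.866 = 6.9%; the first gives practically nothing.

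**5. Drop-out bias.** Large-sample simulation (1.5 million women, r = 0.7, true effect 0.10 m/s). Drop-out depends on baseline speed and on the part of age and 6-minute walk independent of it. Entries are the bias of the baseline-speed-only ANCOVA in completers, across q = 0.02 to 0.20.

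| Dependence on age/6-minute walk beyond baseline speed (odds ratio per SD), exercise / control | Drop-out, exercise / control | Bias (m/s) |
|---|---|---|
| none / none | 30% / 10% | about 0 |
| 2 / 2 | 20% / 20% | about 0 |
| 2 / 2 | 30% / 10% | 0.002 to 0.008 |
| 2 / none | 20% / 20% | 0.003 to 0.008 |
| 3 / none | 25% / 15% | 0.005 to 0.015 |
| 3 / none | 30% / 10% | 0.005 to 0.017 |

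With the extra covariate in the model, the bias is at most 0.0005 m/s in every row. The largest entry is 17% of the 0.10 m/s target and 0.017/0.0261 = 0.65 of a standard error.

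**The case against.** **The stated model is valid.** Baseline-adjusted ANCOVA is a standard primary analysis and already takes most of the available gain: at 60 per arm it lifts power from 77.5% to 88.0% (r = 0.5) or 96.7% (r = 0.7). That almost any model could be made more precise is not a fault. This stands, and is why the point is only an improvement.

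**A reader might infer that the trial is 8 women short (128 against 120) and needs the extra covariates to make this up.** The documents do not support that. The 128 is for an unadjusted t-test. Under ANCOVA the requirement shrinks by about (1 − r²), so 120 suffices once r² exceeds 1 − 120/128 = 0.0625, that is r above 0.25.

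**A reader might infer that the protocol predicts frailty-related loss in the exercise arm, and so a biased result.** It does not. The passages on frailty concern class attendance, adherence and who joins such studies. The 3-month test is separate from the classes, analysis is by intention to treat, and non-attenders get motivational calls. Missing classes is not missing the test. The simulation supposes the unequal pattern, so it shows what could happen, not what is likely.

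**Missing data are already addressed.** The mixed model, multiple imputation and sensitivity analysis are planned, and imputation could include age and the 6-minute walk. This largely stands. The protocol itself notes, however, that the mixed model adjusts only for variables it contains, and no further ones are named.

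**Covariate detail belongs in the analysis plan.** Only in part: the article does state a covariate set, and that choice can be reviewed. The coming analysis plan is the natural place to extend it.

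**Conclusion.** The point holds as a low-severity, free improvement; the protocol contains no error here. For walking speed, adding age and the baseline 6-minute walk would cut the standard error by roughly 1% to 8%, and by 10.6% at the extreme of the assumed range. Power at 0.10 m/s gains about 0.3 to 3 points for q up to 0.10 and r of 0.5 to 0.7. At 0.05 m/s, which was not used for sizing, it gains about 0.6 to 4 points. At q = 0.20 the gains are at most about 6 and 9 points.

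The bias argument is conditional. The shift is about 0.002 to 0.017 m/s in favour of exercise if drop-out depends on these variables beyond baseline speed and acts unequally between arms. It is about zero if drop-out acts alike in both arms or only through baseline speed.

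All these figures rest on assumed correlations and drop-out patterns, and the gain could be close to nothing. They concern walking speed only; nothing was examined for quality of life, fear of falling, grip strength or physical activity.

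**What to change.** For the primary outcome, prespecify before any results by arm are seen: *linear regression of 3-month walking speed with baseline walking speed, age and baseline 6-minute walk distance as covariates and randomised group as factor.*

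- Use the same variables in the mixed model and in the imputation model.
- Fill any missing baseline covariate with its overall mean, so that no randomised woman is dropped for it. The protocol expects few or no missing baseline values.
- Report the ANCOVA with baseline speed alone as a sensitivity analysis.
- Word the change for walking speed only. The present sentence also governs the secondary outcomes, and the 6-minute walk need not be forced into all of those models.

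The cost is one sentence in the analysis plan and two degrees of freedom out of about 117 (120 women less three estimated coefficients). No new data, visits or participants are needed.

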## Discussion

The main purpose of the study is to evaluate the impact of a resistance and balance programme informed by expert panel recommendations for older women with osteoporosis and a history of vertebral fracture. We anticipate that the intervention described will have a positive impact on the primary outcome, 10 m habitual walking speed, as well as secondary outcomes such as HRQOL [3, 18, 23, 24]. Our study has a range of secondary outcomes which can give a broad picture of the women’s health and life situation. The presence of one or more osteoporotic vertebral fractures has a large impact on HRQOL [10], and findings from a 7 year follow up study shows that lowered scores on pain and disability does not fade away unless effective treatment is given [9]. QUALEFFO-41 and SF-36 are outcome measures applied to examine HRQOL and can add valuable knowledge whether exercise can improve HRQOL.

We rely on a systematic approach which corresponds with the guidance on developing and evaluating complex interventions [53]. Several issues related to the quality of the study have to be discussed, such as internal and external validity. Examples of methodological issues that may influence internal validity in a RCT include random allocation, blinding, outcome measures, sample size, drop-outs, statistical methods, and the participants’ adherence to the intervention. In the present study we are particularly concerned with the outcome measures and the participants’ adherence to the programme. Adherence to the programme will be of importance for the internal validity of the study. For some women it can be a challenge to be able to attend to the course twice a week for 12 weeks. In particular this can be challenging for the frailest of the participants. Motivational factors can also affect the adherence. Participants who don’t attend will be followed up with phone calls to motivate and find solutions so they can complete the programme as intended.

Implementation of research into clinical practice is of importance for the overall quality in health research [53]. If the intervention of this present study appears effective, one of its advantages is its applicability in the health care system. The programme requires little equipment, has low material costs and can easily be implemented in community based facilities. The women can perform many of the exercises at home without too much space and equipment to maintain strength and balance after the completion of the programme. The exercise programme can be performed in groups and is therefore more cost effective than one-on-one supervision. The design of group-based stationary circuit session allows the maintenance of the need for individual tailoring. Furthermore, the programme can also be used as a home-based exercise programme under supervision of health care professionals for those who are too fragile to attend to a community based group. Last but not least the exercise programme can also be used as home based“self-training” exercise based on welfare technology/telerehabilitation. The intervention will have potential to promote evidence-based decision-making and empower women with osteoporosis and vertebral fracture to remain in charge of their own lives.

### Limitations

Some limitations of this study should be noted. First, this study evaluates the programme in an urban area, which may limit its generalizability to rural parts and other states with varying demographic characteristics of older adult populations. Second, in this study we don’t recruit people with low walking speed in particular, and it therefore be less likely that we see an effect on the primary outcome. Furthermore, the Hawthorne effect should be considered [54]. Exercise intervention studies appeal to healthier and better-motivated individuals [55]. In this study the intervention is based on an exercise intervention of 12 weeks, twice a week. Frail women with osteoporosis and a history of vertebral fracture in particular may not be able to attend community-based classes twice a week, even though they might benefit even more than healthy women from an exercise intervention. Another limitation is the inclusion criteria, which restrict our findings to individuals living on their own and being free from severe cognitive symptoms. Again the frailest may not be included. General conclusions can only be drawn with caution and no conclusions about training results should be drawn beyond the female osteoporosis population with a history of vertebral fracture living at home. It is a risk of drop-outs and thereby missing data during follow-up. Impact of missing data will be assess with appropriate statistical methods as e.g. linear mixed models, multiple imputations and sensitivity analysis.

### Conclusion

There are a limited number of studies examining the effects of practical exercise programmes on health and quality of life in individuals with osteoporotic vertebral fractures. The proposed study will assess whether an evidence-based multicomponent exercise programme can enhance physical function as well as quality of life for women with osteoporosis and at least one vertebral fracture, as compared to no intervention. Further, the study will assess the effects of the exercise programme immediately post-exercise, and whether they are maintained after cessation. Findings from this study will contribute to the body of evidence available to clinicians to inform the management of people with osteoporotic vertebral fractures.

## Abbreviations

6MWT: 6 Minutes walk test
ADL: Activity of daily life
BMD: Bone mineral density
BMI: Body mass index
DXA: Dual X-ray absorptometry
FES-1: Falls-efficacy scale international
FR: Functional reach
FSST: Four square step test
HRQOL: Health related quality of life
IPAQ-SF: International Physical Activity Questionnaire Short Form
QUALEFFO-41: Quality of life questionnaire of the european foundation for osteoporosis
SF-36: Short form 36
SFT: Senior fitness test
